### Assessments

Participants will complete postal questionnaires at baseline (T0) and at 6 (T1), 12 (T2), and 24 (T3) weeks following recruitment to the study. Two postal reminders will be sent to non-responders. Table 2 provides an overview of the questionnaires that will be completed at each assessment with a rationale for their use. Additionally, those in the intervention group will be asked to record their Walking for Health participation - including date and location of walks attended - on a simple form. Semi-structured telephone interviews will be conducted with ten participants (five per study group) to assess the acceptability of the intervention, randomization, and evaluation of the study methods. At the end of the intervention, a maximum of ten stakeholders (that is, community group coordinators/walk leaders, clinical nurse specialists, research nurses and hospital doctors) will be interviewed by the study researchers (JH, VT) to explore the acceptability of the walking intervention from a professional perspective.

**Table 2 Tab2:** Walking intervention for people with recurrent or metastatic cancer: questionnaire measures by assessment point

Measures included in the study questionnaire	Assessment point			
*Description*	T0 (Baseline)	T1 (6 weeks)^1^	T2 (12 weeks)^1^	T3 (24 weeks)^1^
* Functional assessment of cancer therapy- general* (*FACT-G*) [18]	✓	✓	✓	✓
• *Assesses emotional and physical quality of life in the past 7 days*				
* Depression, anxiety, stress scales* - *21* (*DASS-21*) [19]	✓	✓	✓	✓
• Assesses the frequency and severity of symptoms over the past 7 days				
* General practice physical activity questionnaire* (*GPPAQ*) [20]	✓	✓	✓	✓
• *Assesses physical activity levels (classified as active, moderately active, moderately inactive, inactive) in the past 7 days*				
* Scottish physical activity questionnaire* (*SPAQ*) [21]	✓	✓	✓	✓
• Captures 7-day recall of all leisure and occupational physical activity				
* Spinal cord injury exercise self-efficacy scale* (*ESES*) [22]	✓	✓	✓	✓
• Assesses current exercise self-efficacy				
* Brief fatigue inventory* (*BFI*) [23]	✓	✓	✓	✓
• Assesses severity of fatigue and any impact on functioning in the previous 24 hours				
* Eastern Cooperative Oncology Group* (*ECOG*) [24]	✓	✓	✓	✓
• Measures current performance status, how disease is progressing and affects daily living activities				
* Motivational ruler* [25]	✓	✓	✓	✓

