### Sample size

For the feasibility trial, we aim to consecutively recruit a minimum of 30 patients with recurrent or metastatic cancer to both the control and intervention groups (60 patients in total). A sample size of 30 per arm will be sufficient to estimate the standard deviation of our QoL outcomes and allow estimation of the true treatment difference. The latter is needed to perform a power calculation for the main study. A definitive sample size of a large-scale RCT will be determined from the results of this trial.

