### Data management and analysis

All quantitative data will be double entered and subjected to basic descriptive statistical tests, including calculation of means and frequencies; 95% confidence intervals will be presented to display the imprecision in QoL measures. Independent *t*-tests and χ^2^ tests will be used for two-group measure comparisons. Their paired equivalents will be used to analyze changes in outcome measures between baseline and follow-up. Rates for process measures (for example, recruitment, attrition) will be calculated.

Reasons for non-participation and attrition will be collected to inform future recruitment and retention strategies. We will also collect data on age and gender, with consent, from all eligible people, regardless of whether they choose to participate or not, to explore whether participation rate varies according to these variables.

Audio recordings of interviews will be transcribed verbatim and analyzed using framework analysis; a widely used matrix-based method for collating, reviewing, and understanding qualitative data [26]. All data will be stored securely, and raw data will only be accessible to the study chief investigator (JA) and researchers (JH, VT).

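### None of the stated tests suits the four-level ordered activity scale (GPPAQ): chi-square and its paired forms ignore the ordering, and a t-test treats category codes as an interval scale (minor)

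*Protocol article*

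**What the plan says.** The Data management and analysis section of the protocol article starts from "basic descriptive statistical tests, including calculation of means and frequencies", with 95% confidence intervals for the quality-of-life measures. It then says that independent t-tests and chi-square "tests will be used for two-group measure comparisons", and "Their paired equivalents will be used to analyze changes in outcome measures between baseline and follow-up". It names no paired test, mentions no rank or ordinal method, and does not say which test goes with which measure.

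Table 2 (Assessments) describes the GPPAQ thus: "Assesses physical activity levels (classified as active, moderately active, moderately inactive, inactive) in the past 7 days". It is completed at baseline and at 6, 12 and 24 weeks. The other activity questionnaire, the SPAQ, is described differently: "Captures 7-day recall of all leisure and occupational physical activity". Nothing there says that the SPAQ is categorical.

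The Sample size section sets a minimum of 30 per arm, 60 in all, on the ground that "A sample size of 30 per arm will be sufficient to estimate the standard deviation of our QoL outcomes". It gives no power target.

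**The concern.** With only two families of test named, a four-level ordered result can go to one of two places. Chi-square gives the same answer however the four levels are arranged, so a consistent move from inactive towards active counts no more than a scattered difference of the same size. A t-test on codes 1 to 4 uses the order but assumes equal steps between levels, which nothing in the document supports. Neither chi-square nor its paired forms yields a single effect estimate for a shift along the scale.

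Two of the study's own judgements touch this. The Secondary outcomes section asks how useful self-report is for assessing adherence. The Discussion says the study will judge whether its outcomes can detect change in this population. A test blind to ordering makes it more likely that a usable activity measure looks unresponsive. Only half of each arm receives pedometers (Pedometers section), so the self-report questionnaires are the activity measures planned for everyone in both arms.

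**Working it through.** **Stated figure.** The only figure is the sample size: 30 + 30 = 60, which agrees with the text. No alpha, effect size, SD or dropout is given, so there is nothing further to reproduce. No stated number is wrong.

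**Inputs from the document.** Four ordered levels (Table 2); 1:1 allocation (Design); 30 per arm (Sample size).

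**Assumptions, because the document gives no values.** Two-sided 5% tests; no dropout; control-arm category shares of 0.25/0.25/0.25/0.25, 0.40/0.20/0.20/0.20 or 0.50/0.20/0.20/0.10; a proportional-odds shift with odds ratio 2, 3 or 4. For within-person change: a latent normal variable with correlation 0.6, equal baseline categories, and shifts of 0.3, 0.5 or 0.7 SD.

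**Why ordering matters: one case by hand (equal shares, odds ratio 3).**

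1. Control cumulative odds are 1/3, 1 and 3. Divided by 3 they are 1/9, 1/3 and 1, so the cumulative probabilities are 0.10, 0.25 and 0.50. The intervention shares are therefore 0.10, 0.15, 0.25 and 0.50.
2. Expected counts with 30 per arm: control 7.5, 7.5, 7.5, 7.5; intervention 3, 4.5, 7.5, 15. Half of each column total is 5.25, 6, 7.5 and 11.25.
3. Pearson statistic at these counts, Σ(O−E)²/E = 2 × (2.25²/5.25 + 1.5²/6 + 0 + 3.75²/11.25) = 1.93 + 0.75 + 0 + 2.50 = 5.18, judged against 7.81 (3 df).
4. Mann-Whitney: midranks 5.75, 17, 30.5 and 49.25. Rank sum W = 3×5.75 + 4.5×17 + 7.5×30.5 + 15×49.25 = 1061.25, against a null mean of 30×61/2 = 915. Tie-corrected variance = (900/12) × [61 − Σ(t³−t)/(60×59)] = 75 × (61 − 4.97) = 4202. So z = 146.25/64.8 = 2.26 and z² = 5.09, judged against 3.84 (1 df).

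Nearly all of the signal (5.09 compared with 5.18) lies in the ordered direction, but chi-square must clear a much higher threshold. The implied approximate power is 45% for chi-square (noncentral chi-square, 3 df, noncentrality 5.18) and Φ(2.26 − 1.96) ≈ 62% for the rank test, in line with the simulation below.

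**Between arms, 30 per arm, 20,000 simulated trials per setting (range over the three distributions).**

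| Odds ratio | Chi-square | Mann-Whitney | Gap (points) |
|---|---|---|---|
| 1 (no effect) | about 5% | about 5% | – |
| 2 | about 20% | about 31% | about 11 |
| 3 | 45–47% | 63–64% | about 17–18 |
| 4 | 67–68% | 82–83% | about 15–16 |

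The chance of at least one expected count below 5 ran from 18% to 97%, depending on the assumed shares and odds ratio.

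**Within person, n = 30, 4,000 simulated samples per setting.**

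| Latent shift | Bowker | Stuart-Maxwell | McNemar after splitting 2 v 2 | Signed-rank |
|---|---|---|---|---|
| 0 | 0.5% | 3.4% | 4.4% | 5.0% |
| 0.3 SD | 3% | 16% | 19% | 32% |
| 0.5 SD | 15% | 44% | 45% | 70% |
| 0.7 SD | 43% | 78% | 74% | 93% |

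Bowker's low figures partly reflect sparse cells: it was referred to 6 df throughout and rejected only 0.5% of the time under no change. Stuart-Maxwell is the fairer multi-level comparison.

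**The case against.** The strongest reply is that the article never assigns chi-square to the GPPAQ. Matching tests to measures is detail that a condensed article may leave to a fuller plan, and the Project management section refers to detailed analysis plans. This stands in part. The use of chi-square on the GPPAQ is an inference, and the missing test-by-measure list is not itself the point. What remains is that the methods the article does state include none suited to an ordered scale.

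A reader might go further and infer that the planned paired test cannot be applied, because McNemar's test is for two levels. The document does not support that. It never names McNemar, and Bowker and Stuart-Maxwell handle four levels. The paired wording is unspecific and, on this scale, inefficient; it is not inapplicable.

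A reader might also infer that small expected counts make chi-square invalid here. Its error rate held at about 5% under all three assumed distributions, so the simulations show no such harm. Nor can the point be extended by name to ECOG performance status, since the article does not list its levels or scoring.

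Finally, the loss of power has limited consequence. The primary outcomes are acceptability and feasibility, the sample size has no power target, and no decision in the article turns on a GPPAQ p-value. At odds ratio 2 even the rank test reaches only about 31%. Activity and adherence are also captured by the SPAQ, the intervention group's walk log and the pedometers. All of this stands, and it sets the severity.

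**Conclusion.** The point holds as a minor one about efficiency and estimation. The tests named in the article either discard the ordering of the GPPAQ or impose equal spacing on it. Under proportional shifts at 30 per arm, discarding the ordering costs about 11 to 18 points of power between arms. Within person, a 0.5 SD shift is detected 44% of the time by Stuart-Maxwell and 70% by the signed-rank test. These sizes rest on assumed category shares, odds ratios, latent correlation and full follow-up. They also assume a shift in one direction along the scale; the advantage would shrink or reverse for a change that was not ordered. The consequence is confined to how the study judges the usefulness and responsiveness of one self-report measure. It does not affect the primary outcomes or the quality-of-life variability estimates.

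**What to change.** Add a sentence or two to Data management and analysis. For the GPPAQ, and any other outcome scored in ordered categories:

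- **Between arms:** fit a proportional-odds model of the follow-up category on arm, with the baseline category entered as a single score, and report the common odds ratio with its 95% CI. This takes five parameters (three thresholds, arm, baseline score), against seven if the baseline is entered as four categories. If the data are too sparse for the model, use an unadjusted Mann-Whitney test, recognising that it neither adjusts for baseline nor gives a common odds ratio.
- **Change within person:** use a signed-rank test together with a baseline-by-follow-up table.
- **Nominal and binary items:** keep chi-square or Fisher's exact test.

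No new data are needed. The small cost is the proportional-odds assumption. The simulations compared unadjusted tests only, so they show the gain from using the ordering and not any further gain from baseline adjustment. The signed-rank test ranks changes by the number of levels moved, so the table should be read with it.

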### Serious adverse events reporting and monitoring

It is not anticipated that there will be any risk to participants. With permission, the researchers will write to all participants GPs to inform them of their participation on the study. Data on unexpected and serious adverse events will be collected at assessments T1 and T2. Any serious adverse events deemed to be related to the intervention or due to participation in the study will be reported to the chief investigator within 24 h of the team learning of its occurrence.

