### Setting and participants

The study will be undertaken in two large London NHS Foundation Trusts. Participants are eligible for the study if they i) are 16 years or over, ii) have a diagnosis of breast, colorectal, upper gastrointestinal, gynecological, hematological, head and neck, melanoma, or prostate cancer with recurrent or metastatic disease, iii) meet the eligibility criteria for specific cancer diagnoses (Table 1), and iv) are able to walk for a minimum of 30 min unaided. Exclusion criteria are i) having bone metastases which the responsible health-care professional considers a contraindication to participating in the walking intervention; and ii) unable to speak and understand English.

**Table 1 Tab1:** Walking intervention for people with recurrent or metastatic cancer: definitions of recurrent or metastatic disease

Primary tumor	Definition
Breast	Metastatic disease - stage 4, for example, visceral, bone, soft tissue, and so on.
	Not local recurrence
Colorectal	Metastatic - stage 4 - M1
Gynecological	Ovary - symptomatic stage 3/4/recurrence
	Cervix - stage 3/4
	Endometrial - stage 3/4
	Vulva - stage 3/4
Hematological	Lymphoma (high and low grade) within first 6 months of relapse, myeloma
Head and neck	Metastatic disease, recurrence
Melanoma	Stage 3/4
Prostate	Distant metastatic disease or bone metastases (T3, N1, M1)
Upper gastrointestinal	Stage 3/4, oesophago-gastric

Figure 1 shows the flow of participants through the study. Participants will be screened for eligibility by their health-care professional (that is, nurses or doctors) as they visit clinics or via hospital records. Health-care professionals or researchers will describe the study to those identified during a clinic attendance and where appropriate provide a study information pack comprising an invitation letter, information sheet, permission to contact form, a unique study identification number, and postage paid envelope. Those identified via hospital records will be sent the study information pack by post by their health-care professionals. Health-care professionals/researchers will record reasons for ineligibility and reasons for declining participation.

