• Includes two visual 100 mm visual analog scales to measure current importance and confidence in walking				
* Patient reported demographics and clinical history*	✓			
• Study specific measure includes sex, age, marital status, education, long-standing health conditions etc.				
* Adverse outcomes and events* (*intervention only*)		✓	✓	
* End of study questionnaire*				✓
• Effects on quality of life (intervention only); usefulness of information; achievement of physical activity goals; satisfaction with study/intervention; free text comments about the study				

^1^Randomization occurs after the baseline questionnaire has been returned. Therefore, follow-up questionnaire timings are as follows: *control group* - from the date of the post-randomization telephone call (for example, informing them they are in the control); *intervention group* - from the date of the motivational interview telephone call.

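### The only serious adverse event collection described is a self-completed postal form at weeks 6 and 12, so fatal or incapacitating events are liable to be missed or learned of late

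*Protocol article*

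**What the plan says.** The section on serious adverse events fixes when the data are gathered: "Data on unexpected and serious adverse events will be collected at assessments T1 and T2". The Assessments section says what those time points are: "Participants will complete postal questionnaires at baseline (T0) and at 6 (T1), 12 (T2), and 24 (T3) weeks following recruitment to the study". Table 2, whose left-hand column is headed "Measures included in the study questionnaire", lists "Adverse outcomes and events" as one of those items. It is ticked at T1 and T2 and marked for the intervention group only. The footnote to Table 2 starts the follow-up clock at the motivational interview call in the intervention group and at the post-randomization call in the control group.

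Non-responders get two reminders, both by post. Three other contacts are described, none of them as a route for reporting events:
- The GP letter, sent with the participant's permission, tells the GP that the patient is in the study.
- Reasons for attrition are gathered (Data management and analysis), for the stated purpose of planning recruitment and retention.
- The research team meets weekly (Project management), on timescale, adherence and data plans.

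A serious event judged related to the intervention or to taking part "will be reported to the chief investigator within 24 h of the team learning of its occurrence".

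**The concern.** The person asked to report the event is the person it has happened to, by post, up to six weeks later. That works for a minor injury. It works poorly for an admission with lasting incapacity, and it cannot work for a death. Reminders posted to the same address do not help.

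The trial is meant to show whether the intervention is acceptable and whether a full trial is warranted. A short list of events drawn from those well enough to post a form could be read as evidence that walking is safe in advanced cancer, when part of the reason for the short list is how it was compiled.

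**Working it through.** The article states no event count or rate on this point, so there is no figure to reproduce. Two things can be worked out: the delay built into the schedule, and the direction of the error.

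**Delay to the next scheduled enquiry**

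Inputs: safety enquiries at weeks 6 and 12 (Assessments; safety section), with the clock starting at the post-randomization or motivational interview call (Table 2 footnote).
- Interval between enquiries: 6 weeks × 7 = 42 days.
- Range of wait: 0 days (event just before the form) to 42 days (event just after the previous one).
- Mean wait, if events are spread evenly over each interval: 42 / 2 = 21 days.
- An event in the first week waits 42 − 7 = 35 to 42 days.
- Postal and reminder time comes on top. The article does not state it.

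If the week 6 form is not returned but the week 12 form is, an event in the first interval waits 42 to 84 days. This assumes that the week 12 form asks back that far.

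**Direction of the error**

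Let *e* be the true proportion of participants with a serious event, *r₁* the probability that such a participant returns the form, and *r₀* the probability for the others.
- Proportion of all events recorded by this route = *r₁*.
- Proportion with an event among returned forms = *r₁e* / [*r₁e* + *r₀*(1 − *e*)]. This is below *e* whenever *r₁* < *r₀*.
- For a participant who has died before the form is due, *r₁* = 0.

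The observed figure is therefore too low as soon as return is less likely after a serious event. None of *e*, *r₁* and *r₀* appears in the article, so the size of the shortfall cannot be derived from it.

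**The case against.** The strongest reply is that this is a condensed article. It says that events are collected at T1 and T2; it does not say that nothing else is done. Spontaneous reports, clinic reports and walk leaders could all bring an event to the team, and a fuller protocol may provide for them. This stands as a limit on the wording: the postal form is the only collection described, and it cannot be called the only one that exists. It does not remove the point, because the method that is stated has this weakness when followed as written.

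A reader might infer four stronger things, which the document does not support:
- **That the 24-hour rule fails.** Its clock starts when the team learns of the event, by whatever route, so it can be met every time. The weakness is the time before the team knows.
- **That the section contradicts the eligibility criteria.** It says "It is not anticipated that there will be any risk to participants", while patients are excluded for "having bone metastases which the responsible health-care professional considers a contraindication to participating in the walking intervention". The first sentence concerns those who remain after that screen. It may be optimistic, but the two are compatible.
- **That an unreturned form is simply lost.** Reasons for attrition are collected, and death or illness is an obvious reason. They are not described as safety data, which is a smaller fault and an easy one to mend.
- **That the under-count can be given as a percentage.** Any such figure would rest on assumed event and return rates.

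It is also fair that many serious events in this population will come from the cancer. A shortfall in all-cause events does not measure a bias about harm from walking.

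**Conclusion.** The concern holds in a limited form. As described, serious events reach the study through a form that depends on the participant being alive and well enough to return it, and postal reminders are the only follow-up of non-return. Deaths and incapacitating events are liable to be missed or learned of late, and the record leans towards no harm.

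The delay of 0 to 42 days, mean 21, rests on even spread of events and prompt return of the form. The direction rests on one assumption, that return is less likely after a serious event. The size is unknown. The point is worth acting on because the gain in safety data is concrete and the cost small; it does not undermine the feasibility aims.

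**What to change.** In the section on serious adverse events:
1. Add to the planned GP letter, and to the information given to participants in both arms, a request that deaths, admissions and falls or fractures be reported to the team when they occur. The participant information matters because the letter goes only where permission is given.
2. Count any death, admission or injury found as a reason for attrition as a serious adverse event, under one rule for both arms. Table 2 limits the adverse event item to the intervention group and the safety section does not, so the two must be reconciled for this to work.
3. Report events alongside the number of forms not returned, by arm and time point.
4. Where consent covers it, check vital status and admissions in hospital records on the same basis for all participants. Checking only those who did not return a form would apply different sources to the two groups.

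**Cost.** A sentence in an existing letter, a line in the participant information, a little extra site time and a higher reported event count. The Ethics and dissemination section requires planned changes to go for approval.

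**Timing.** Recruitment closed on 30 November 2014. A clock started that day reaches week 12 (84 days) on 22 February 2015, before publication on 12 March 2015; later calls would shift this somewhat. In this trial, items 2 and 3 remain practical, and item 4 where consent already allows it. Item 1 comes mostly too late for the T1 and T2 window here and should be carried into any main trial.
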